## Abstract

**Background:**

Rheumatoid arthritis (RA) and spondyloarthritis (SpA) are chronic inflammatory rheumatic diseases characterised by pain, fatigue, mood disturbances, sleep problems and reduced quality of life. These symptoms are highly variable both between individuals and within individuals across days, reflecting the fluctuating nature of disease activity and daily functioning. Although physical activity is known to alleviate many of these symptoms, individuals with RA and SpA often encounter barriers that limit regular engagement. Capturing the dynamic interplay between symptoms and physical activity therefore requires methods that account for day-to-day and moment-to-moment variability. Ecological momentary assessment (EMA), especially when combined with actigraphy, enables real-time, context-sensitive monitoring of symptoms and physical activity in daily life. However, little is known about the feasibility and acceptability of such protocols in individuals with RA and SpA, for whom participant burden and adherence may represent significant challenges. This pilot study therefore aims to assess the feasibility and acceptability of a 14-day EMA protocol and to explore factors associated with objectively measured physical activity in individuals with RA and SpA.

**Methods and analysis:**

50 adults diagnosed with RA or SpA will be recruited through rheumatology clinics or via advertisement. Eligible participants must be smartphone users without cognitive or physical impairments affecting participation. After providing consent, participants will complete baseline questionnaires regarding disease activity, quality of life, sleep, pain, fatigue, affective states and will attend a remote session with a member of the research team to learn how to use the mobile app. They will then complete a 14-day EMA protocol, during which data on patient-related outcomes (PROs), including pain, fatigue, sleep quality and affective states (i.e. positive and negative affects) will be assessed four times daily: upon awakening, 11:00, 15:00 and 20:30. Physical activity and sleep will be continuously monitored using both a wrist-worn and a thigh-worn device. Feasibility will be evaluated based on adherence to EMA prompts and actigraphy wear time. Acceptability will be assessed via a study-specific questionnaire and qualitative interviews conducted at the end of the protocol. Exploratory analyses will examine real-time, temporal and lagged relationships between PROs (pain, fatigue affective states), sleep and physical activity levels.

**Ethics and dissemination:**

This study was approved by the French national ethics committee [*Comité de protection des personnes Nord Ouest I, 2025-A01349-40*] on 24/07/2025. The results will be disseminated in peer-reviewed journals and at international conferences.

**Trial registration number:**

NCT07167784.

STRENGTHS AND LIMITATIONS OF THIS STUDYThis study uses concurrent ecological momentary assessment and wrist-worn and thigh-worn actigraphy to capture sleep and physical activity in real-world conditions.A 14-day intensive repeated-measures design enables within-person analysis using both subjective and objective measurements.The pilot feasibility design and limited sample size restrict the scope of analyses and generalisability of findings.The protocol was co-developed with a patient research partner to optimise the clarity and feasibility of EMA items.The remote, technology-based design with frequent assessments may increase participant burden and limit inclusion of individuals with low digital literacy.

## Introduction

 Patient-reported outcome measures (PROs), including pain, fatigue, mood and sleep quality, are major determinants of reduced quality of life in individuals with rheumatoid arthritis (RA) and spondyloarthritis (SpA).^1 2^ These chronic conditions affect the joints and surrounding tissues and are characterised by symptoms that fluctuate markedly within and between days.^3^,^6^ Pain, fatigue and sleep disturbances frequently co-occur and interact dynamically, influencing patients’ daily functioning and levels of physical activity.^7 8^ As a result, the burden of RA and SpA is not only defined by average symptom levels but also by their day-to-day variability and temporal interactions, which are insufficiently captured by traditional cross-sectional or clinic-based assessments.

In addition to pharmacological treatments, such as nonsteroidal anti-inflammatory drugs and conventional or biological disease-modifying antirheumatic drugs, regular physical activity (PA) and reduced sedentary behaviour are strongly recommended for patients with RA and SpA.^9^,^11^ Current European League Against Rheumatism guidelines emphasise regular PA as a core component of disease management due to its beneficial effects on pain, physical function, mobility and disease activity.^12^,^16^ However, despite these established benefits, many patients struggle to maintain regular PA in daily life, with pain, fatigue and sleep disturbances commonly reported as major barriers.^17^,^19^ Understanding how fluctuations in symptoms relate to everyday activity patterns in real-world settings is therefore essential to identify periods of vulnerability and opportunity and to inform more personalised and adaptive PA interventions.

Most existing studies have relied on retrospective symptom assessments (eg, questionnaires), which fail to capture the day-to-day variability in PROs progression and PA levels. Ecological Momentary Assessment (EMA), which involves repeated real-time data collection via mobile applications, reduces recall bias and enhances the ecological validity of data, particularly those related to PROs.^20^ When combined with actigraphy, EMA enables a fine-grained understanding of the dynamic interactions between PROs and PA in daily life. Although this combined approach has been applied in other chronic diseases,^21 22^ it has not yet been explored in patients with RA and SpA.

Although EMA provides numerous advantages, its implementation also presents challenges.^23^ Maintaining participant adherence and managing the burden of frequent prompts can lead to response fatigue and habituation effects.^24^ Suboptimal adherence to the EMA protocol not only generates missing data but may also compromise study outcomes. A meta-analysis of 68 EMA studies on health-related behaviours in adults reported an average adherence rate of 82%, with considerable variability ranging from 38% to 98%.^25^ This variability highlights the importance of evaluating feasibility and adherence within specific clinical populations and study designs before large-scale implementation. In this context, feasibility refers to the extent to which study procedures can be successfully implemented in real-world conditions with the target population, typically assessed through recruitment and retention rates, adherence to repeated assessments and participant acceptability. Given this variability, it is essential to evaluate the feasibility and acceptability of EMA protocols in specific populations before large-scale implementation. This pilot study aims to assess the feasibility and acceptability of a 14-day EMA protocol combined with actigraphy in patients with RA and SpA. The secondary objectives of this study are: (1) to examine the temporal relationships between pain, fatigue and sleep, considering their reciprocal influences and variations across different times of the day; (2) to describe both the immediate and lagged effects of these factors on objectively measured physical activity; (3) to compare adherence to and acceptability of two actigraph devices assessing physical activity, sleep and sedentary behaviour, worn at two different body sites (non-dominant wrist vs thigh) and (4) to explore the qualitative determinants of protocol acceptability directly from the patients’ perspective.

## Materials and methods

### Study design and setting

The **D**aily s**Y**mptom a**N**d phys**I**c**A**l activity **M**onitoring In **C**hronic inflammatory rheumatic diseases (DYNAMIC) study is a prospective, observational, 14-day study conducted entirely remotely. Data will be collected using actigraphy and repeated questionnaires delivered via a mobile application.

Participants will wear two actigraphy devices (Actigraph GT3X, Actigraph, Pensacola, FL, USA and SENS motion, SENS, Copenhagen, Denmark) continuously for 14 days, while completing EMA surveys four times per day via the Avicenna Research App (Avicenna Research, Toronto, Canada).

Upon providing consent, participants will be enrolled in the study. Actigraphy devices will be mailed to them, and a meeting will be scheduled upon receipt. During this session, participants will complete baseline questionnaires online.

Participants will then be instructed to continuously wear two actigraphy devices (Actigraph GT3x and SENS motion) and to complete EMA surveys via the Avicenna Research app (Avicenna Research, Toronto, Canada). To optimise engagement and adherence, the EMA protocol will incorporate a gamification component specifically designed to increase response rates.^26^ At study initiation, participants will complete a conditional item assessing their usual wake-up time (selectable between 5:30 a.m. and 10:30 a.m.). Based on this response, the first EMA survey will be scheduled at wake-up time plus 30 min. Subsequently, four fixed-time daily surveys will be administered: upon awakening, at 11:00 a.m., 3:00 p.m. and 8:30 p.m. Participants will be instructed to complete each survey immediately upon receiving the notification. Non-response will trigger up to three reminder notifications at 15 min intervals, after which the survey will expire and disappear.

Upon completion of the 14-day protocol, participants will return the actigraphy devices using a prepaid envelope provided by the study team, complete an end-of-study questionnaire assessing study acceptability and be invited to participate in a qualitative interview with a member of the research team.

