### Outcomes

#### Primary outcomes

The primary outcomes are feasibility and acceptability.

**Feasibility** will be evaluated through: (1) attrition rates: measured by the number of participants who withdrew from the study, (2) EMA response rate: the number and percentage of data collected from EMA surveys relative to the number of potential assessments, as well as the latency between the prompt and participants' response, (3) actigraphy adherence (the threshold is ≥21 hours of wear time per 24 hours across the 14-day protocol).^27^

**Acceptability** will be assessed using a study-specific questionnaire and qualitative interviews. Quantitative indicators will include participant satisfaction, perceived relevance, ease of use and daily burden associated with EMA and actigraphy use.^27 28^ Responses will be rated on a five-point Likert scale (1=strongly disagree to 5=strongly agree). An item will be considered validated if the participant’s score is ≥3/5. Item-level acceptability will be defined as ≥70% agreement for positively worded items and ≤30% agreement for negatively worded items. During the interviews, the interviewer will take notes and, with the participant’s prior consent, audio-record the session. These recordings will be transcribed in a non-verbatim format and analysed using content analysis to identify recurring themes.

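### For the latest permitted wake-up times, the morning survey coincides or overlaps with the fixed 11:00 survey

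*Protocol article*

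**What the plan says.** All scheduling figures are in the protocol article, Study design and setting.

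- At study start each participant gives a "usual wake-up time (selectable between 5:30 a.m. and 10:30 a.m".
- From that answer, "the first EMA survey will be scheduled at wake-up time plus 30 min".
- The next sentence describes the day differently: "four fixed-time daily surveys will be administered: upon awakening, at 11:00 a.m., 3:00 p.m. and 8:30 p.m".
- On unanswered prompts: "Non-response will trigger up to three reminder notifications at 15 min intervals, after which the survey will expire and disappear".

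Under Primary outcomes, feasibility includes "the number and percentage of data collected from EMA surveys relative to the number of potential assessments" and "the latency between the prompt and participants' response". Secondary outcomes rest on immediate and lagged associations and on variation across the day. Under EMA assessments, pain, fatigue and affect are asked at all four prompts, and sleep quality in the morning only.

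The article gives no minimum spacing between prompts, does not move the 11:00 prompt for late wakers, and does not say which survey takes precedence when two are open.

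**The concern.** The morning prompt moves with the participant's answer and the second prompt does not. At the late end of the permitted range the two meet. A late waker can then have two surveys open that share the pain, fatigue and affect items.

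Three things are at stake for that participant:

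- **Response rate.** If one of the pair is left unanswered because the other has just been completed, the loss counts as non-adherence in a primary feasibility measure, although the schedule produced it.
- **Lag.** The interval from the morning to the second assessment becomes very short or zero, so it carries little or no temporal information.
- **Sleep rating.** If the morning survey is the one left to expire, that day's only EMA sleep rating is lost.

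The Statistical analysis section plans to describe response by time interval, and Potential implications says the findings will guide prompt frequency and timing. A clash at one time slot could be read there as low engagement.

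**Working it through.** The plan gives no figure of its own to reproduce on this point. The check is clock arithmetic.

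**Inputs**

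- Selected wake-up time W: 05:30 to 10:30, a range of 300 min (Study design and setting).
- Offset to the morning prompt: 30 min (same section).
- Second prompt: 11:00. Later prompts: 15:00 and 20:30 (same section).
- Response window L: 3 × 15 = 45 min if the survey closes at the last reminder, or 4 × 15 = 60 min if one more interval follows. The article does not settle which, so both are shown.
- Duration 14 days, 4 prompts a day, 50 participants.

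**Formulas**

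- Morning prompt = W + 30 min
- Gap = 11:00 − (W + 30 min)
- Overlap = max(0, W + 30 min + L − 11:00)

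| W | Morning prompt | Gap to 11:00 (min) | Overlap, L = 45 (min) | Overlap, L = 60 (min) |
|---|---|---|---|---|
| 05:30 | 06:00 | 300 | 0 | 0 |
| 09:30 | 10:00 | 60 | 0 | 0 |
| 09:45 | 10:15 | 45 | 0 | 15 |
| 10:00 | 10:30 | 30 | 15 | 30 |
| 10:15 | 10:45 | 15 | 30 | 45 |
| 10:30 | 11:00 | 0 | 45 | 60 |

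**Threshold for overlap.** W > 11:00 − 30 min − L, that is W > 09:45 for L = 45 and W > 09:30 for L = 60. As a share of the selectable clock range this is 45/300 = 15% or 60/300 = 20%.

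**First daily lag among those affected.** It is below 45 min for L = 45 (30, 15 or 0 min at quarter-hour selections) and below 60 min for L = 60. The later lags are 11:00 to 15:00 = 240 min and 15:00 to 20:30 = 330 min.

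**Other reading of the morning prompt.** If it were sent at the wake-up time itself (offset 0), the gap at 10:30 would be 30 min. Overlap would begin only after 10:15 (L = 45) or 10:00 (L = 60). The exact coincidence disappears, but the overlap does not.

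**Worst case for one participant.** Potential assessments: 14 × 4 = 56. If one of each overlapping pair is missed on all 14 days, 56 − 14 = 42 remain, and 42/56 = 75%.

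**Effect on the pooled rate.** Total potential assessments: 50 × 56 = 2,800. Each fully affected participant loses at most 14, and 14/2,800 = 0.5 percentage points. For an assumed 1, 3, 5 or 10 such participants, the maximum fall is 0.5, 1.5, 2.5 or 5.0 points.

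**The case against.** The strongest reply concerns consequence, since the arithmetic is not in dispute.

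- **Few may be affected.** The 15–20% is a share of clock options. A reader might take it as a share of participants, but the article gives no wake-time distribution and the number could be zero. This stands.
- **The 75% is a ceiling on harm.** It needs one of the pair to be missed on every one of 14 days, and nothing in the article says the app prevents answering both. Exact coincidence occurs only at 10:30. Someone who selects 10:00 has the morning survey alone for 30 min and is told to answer at once. This stands.
- **No threshold is crossed.** A reader might set 75% against the 82% average adherence in the Introduction and infer that feasibility would be judged a failure. That 82% is background, with a quoted range of 38% to 98%, and Primary outcomes sets no response-rate threshold. The inference is not supported.
- **The surveys can be told apart, and latency stays defined.** The morning survey also carries the sleep item, and latency is measured from each survey's own prompt. It is therefore too strong to say that the pooled results are corrupted.
- **Unequal spacing comes with any wake-anchored prompt.** An analysis plan can handle it. This is fair for moderate differences, but a zero gap leaves nothing to model as a lag.
- **App settings belong in a fuller document.** A condensed article may omit precedence rules. However, this article states the permitted range, the offset and a fixed 11:00 prompt, and those three figures conflict without reference to any omitted detail.

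**Conclusion.** The clash is real and follows from the article's own figures. It is exact at a selected wake-up time of 10:30, and the windows overlap after 09:45 with a 45-min window or after 09:30 with an assumed 60-min window. For those participants, schedule-caused non-response can enter a primary feasibility measure, and the first daily lag loses most or all of its meaning.

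It is a boundary-case error of minor to moderate weight. The pooled bound assumes 50 participants contributing all 56 prompts and one lost survey per pair per day. The documents do not support a claim that the study's overall feasibility result is compromised, and they give no way to say how many people are affected.

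The two descriptions of the morning prompt (30 min after usual waking, or on awakening) also need to be made one.

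**What to change.** 1. **App schedule.** For participants whose morning window would reach 11:00, delay the second prompt to a fixed minimum interval after the morning prompt, at least the full response window. Leave 15:00 and 20:30 unchanged. In the extreme case (W = 10:30) the second prompt moves to 11:45 with a 45-min window or 12:00 with a 60-min window, which leaves 195 or 180 min to the 15:00 prompt.
2. **Wording.** State the response window, and describe the morning prompt as usual wake-up time plus 30 min wherever it is now described as on awakening, including the abstract.
3. **Participants already enrolled with overlapping windows.** Keep the primary response rate on all scheduled prompts. Add a sensitivity response rate that counts each overlapping pair as one occasion. In the lag analysis, use actual response timestamps or exclude the overlapping pair. Fix these rules before the analysis, which the article places after follow-up is complete.

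Two simpler remedies are worse. Capping the selectable time at 09:30 would prompt a true 10:30 waker at 10:00, while asleep; with a 45-min window the survey would close at 10:45. Removing overlapping prompts from the primary denominator would redefine a primary outcome while the study is running.

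**Cost.** One app rule, a clarified sentence and one extra sensitivity analysis. The second prompt is no longer at 11:00 for a few late risers. Because recruitment began on 19 November 2025, late risers enrolled before and after the change would have different schedules, which should be reported.

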### Sample size

This is a pilot study of feasibility and acceptability, without a quantitative primary outcome measure. As such, a formal sample size calculation is not required. In accordance with recommendations and considering what is reasonable and feasible, we estimate that recruiting 50 participants will provide sufficient variability to assess the feasibility and acceptability of the study.^29 30^ This sample size estimate accounts for an anticipated attrition rate of approximately 20%.

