#### End of study assessments

Participants will complete the end-of-study questionnaire (online supplemental file 2) and participate in an end-of- study qualitative interview after the 14-day EMA collection period (online supplemental file 3).

Any adverse events relating to the use of technology or participating in the study will be recorded. Any serious adverse events will be reported to the sponsor.

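### As described, acceptability is collected at the end of the 14 days with no provision for participants who stop early, so the 70%/30% item rules would rest on completers while about 20% attrition is expected

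*Protocol article*

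**What the plan says.** The article sets the timing of the acceptability assessment in two places. Under Study design and setting, the sequence opens with "Upon completion of the 14-day protocol, participants will return the actigraphy devices"; participants then "complete an end-of-study questionnaire assessing study acceptability and be invited to participate in a qualitative interview". Under End of study assessments, "Participants will complete the end-of-study questionnaire" and take part in the interview "after the 14-day EMA collection period". Neither section mentions people who withdraw before day 14.

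The decision rule is under Primary outcomes: "Item-level acceptability will be defined as ≥70% agreement for positively worded items and ≤30% agreement for negatively worded items". No denominator is given. On scoring, the same section says: "An item will be considered validated if the participant’s score is ≥3/5".

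Under Sample size, "we estimate that recruiting 50 participants will provide sufficient variability to assess the feasibility and acceptability of the study", and "This sample size estimate accounts for an anticipated attrition rate of approximately 20" per cent.

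The Statistical analysis section says that feasibility and acceptability will be summarised over the whole study population. For people who leave, the article plans a count of withdrawals, a flow diagram with reasons, and a qualitative analysis of those reasons. None of these yields an item rating.

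**The concern.** Acceptability is one of the two primary outcomes, and it is judged by a fixed pass mark for each item. Ratings requested only when the 14 days are complete come from people who tolerated the procedures to the end.

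The article itself gives grounds for expecting this group to differ from those who leave. The Introduction links frequent prompts to burden and response fatigue. Potential implications says that the intensity of EMA may lead to attrition. Daily burden is also one of the listed acceptability indicators. If burden causes some withdrawals, being in the rated group depends partly on the quantity being rated, and agreement among completers overstates agreement among all who took part.

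The results are meant to guide the design of a larger study. The secondary objectives on device acceptability and on the qualitative determinants of acceptability would lose the same informants. This is about when data are collected: a later analysis plan can choose a denominator, but it cannot recover ratings that nobody requested.

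**Working it through.** **Inputs.** Enrolled: 50 (Sample size). Anticipated attrition: about 20% (Sample size). Pass marks: at least 70% agreement for positive items, at most 30% for negative items (Primary outcomes). Agreement among drop-outs: not in the article, so an assumed range is used.

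**The plan's own figure.** There is no formal calculation to reproduce. The figures are consistent with 50 × (1 − 0.20) = 40 completers, and 40 / (1 − 0.20) = 50. The base of 40 is implied, not stated.

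**Positive items.** If *a* of 40 completers agree and a proportion *q* of the 10 drop-outs would agree, agreement among all enrolled is (*a* + 10*q*) / 50.

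| Assumed *q* | Item at 28/40 (70%) | Item at 32/40 (80%) |
|---|---|---|
| 0% | 28/50 = 56% | 32/50 = 64% |
| 20% | 30/50 = 60% | 34/50 = 68% |
| 30% | 31/50 = 62% | 35/50 = 70% |
| 40% | 32/50 = 64% | 36/50 = 72% |
| 70% | 35/50 = 70% | 39/50 = 78% |

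For the 80% item the break-even is 32 + 10*q* = 35, so *q* = 0.30. It fails among all enrolled only below that value.

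**Negative items.** An item passes among completers at 12/40 = 30%. If a proportion *r* of drop-outs would agree, the overall figure is (12 + 10*r*) / 50: 15/50 = 30% at *r* = 30%, and 22/50 = 44% at *r* = 100%.

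**Other attrition rates, worst case (*q* = 0).** At 10% attrition there are 45 completers, the smallest passing count is 32, and 32/50 = 64%. At 30% there are 35 completers, the smallest passing count is 25, and 25/50 = 50%.

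**Chance of passing, as an illustration.** Suppose true agreement is 75% in completers and 30% in drop-outs. Overall agreement is 0.8 × 0.75 + 0.2 × 0.30 = 66%, below the mark. Completers alone still reach 28/40 with binomial probability 0.82.

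**Denominator.** Study design and setting enrols people at consent, before the devices are mailed, so some of the 10 may leave without using anything they could rate. If, for illustration, 5 of the 10 left before starting, 45 people started. The item at 28/40 then has a worst case of 28/45 = 62%, and the item at 32/40 has a worst case of 32/45 = 71%, still a pass. The table therefore shows the largest effect at 20% attrition.

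**The case against.** A reader might infer that drop-outs are barred from the questionnaire. The article does not say so. The timing under End of study assessments can be read as calendar time for everybody, and the promise to summarise the whole study population fits that reading. This is also a condensed article, and an exit procedure may stand in the full protocol. All this holds, and it limits the point to what is described. Against it, Study design and setting ties the questionnaire to completing the protocol, and the article mentions no other route.

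A reader might also infer that passing items would turn into failures. The arithmetic does not support that in general. An item at 80% of completers needs fewer than 30% of drop-outs agreeing, and no document supports a value that low. If the 3/5 cut also defines agreement, mid-scale answers count as agreement, which makes very low values less plausible still.

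People may leave for reasons unrelated to acceptability, such as a flare or a phone problem. If drop-outs would agree as often as completers, there is no bias. Attrition is also reported in its own right, as one of three components of feasibility, with reasons, so the loss stays visible. These points stand too. However, attrition does not enter the 70% rule, and the design as described cannot show whether drop-outs and completers agree equally often.

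**Conclusion.** The point holds in a limited form. As described, acceptability ratings come at the end of the protocol, no provision is made for those who stop early, and the promised summary for the whole study population could not be produced from such data if about 20% leave. That completers are favourably selected is a reasonable expectation on the article's own account of burden, but not an established fact.

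The consequence is material for items near the pass mark: an item just passing at 70% of completers represents 56% to 70% of those enrolled, for assumed drop-out agreement of 0% to 70%. It is smaller for items well above the mark, and smaller again if some of the anticipated attrition occurs before participants start. This is a cheap improvement worth making, not a defect that invalidates the study.

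**What to change.** 1. Send the same online questionnaire and the interview invitation to every participant who started, at day 14 or on stopping, whichever comes first. If this is already the practice, one sentence saying so is enough.
2. State the denominator of the 70%/30% rules: all who started and responded, whether or not they finished.
3. Beside it, give the completers-only percentage and a sensitivity bound that counts non-respondents as not agreeing with positive items and as agreeing with negative items.

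The bound should not be the primary result. With 10 non-respondents out of 50 it would require 35/40 = 87.5% of completers on a positive item and at most 5/40 = 12.5% on a negative item, and it merges attrition with acceptability, which the article reports separately.

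**Cost.** An existing form goes out earlier to about 10 people (50 × 0.20), and a sentence or two is added to the plan. It is a small procedural change in a running study: recruitment began on 19 November 2025, with the target expected by the end of March 2026, under an ethics approval already given. Some withdrawers will not reply or have already left, and the acceptability figures may be slightly less favourable. The denominator can still be fixed before analysis, which is planned only after inclusion and follow-up are complete.
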